## Abstract

**Background:**

We present a study protocol for a randomized, double-blind, placebo-controlled trial that investigates the hypothesis if intervention in the symptomatic phase preceding clinical arthritis (clinically suspect arthralgia (CSA)) is effective in preventing progression from subclinical inflammation to clinically apparent persistent arthritis. Currently, rheumatoid arthritis (RA) can be recognized and diagnosed when arthritis (joint swelling) has become detectable at physical examination. Importantly, at this time, the immune processes have already matured, chronicity is established, and patients require long-standing treatment with disease-modifying anti-rheumatic drugs. The TREAT EARLIER trial studies the hypothesis that intervention in the symptomatic phase preceding clinical arthritis is more often successful in permanent disease modification because of less matured underlying disease processes.

**Methods:**

A two-level definition to identify patients that are prone to develop RA is used. First, patients should have CSA and recent-onset arthralgia (< 1 year) that is suspect to progress to RA according to the expertise of the treating rheumatologist. Second, patients need to have subclinical inflammation of the hand or foot joints at 1.5 T MRI. The trial aims to recruit 230 participants from secondary care hospital settings across the south-west region of The Netherlands. Intervention will be randomly assigned and includes a single-dose of intramuscular 120 mg methylprednisolon followed by methotrexate (increasing dose to 25 mg/week orally) or placebo (both; injection and tablets) over the course of 1 year. Thereafter, participants are followed for another year. The primary endpoint is the development of clinically detectable arthritis, either fulfilling the 2010 criteria for RA or unclassified clinical arthritis of ≥ 2 joints, which persists for at least 2 weeks. DMARD-free status is a co-primary endpoint. The patient-reported outcomes functioning, along with workability and symptoms, are key secondary endpoints. Participants, caregivers (including those assessing the endpoints), and scientific staff are all blinded to the group assignment.

**Discussion:**

This proof-of-concept study is the logical consequence of pre-work on the identification of patients with CSA with MRI-detected subclinical joint inflammation. It will test the hypothesis whether intervention in patients in this early phase with the cornerstone treatment of classified RA (methotrexate) hampers the development of persistent RA and reduce the disease burden of RA.

**Trial registration:**

Dutch Trial Register NL4599 (NTR4853). Registered on 20 October 2014

## Introduction

### Background and rationale {6a}

Rheumatic and musculoskeletal diseases (RMDs) are among the most prevalent, disabling, and burdensome non-communicable diseases in Europe and the USA, eliciting high costs for healthcare and social security budgets. RMDs are also the number one cause of disability in Europe. Rheumatoid arthritis (RA) is the commonest inflammatory cause of disability. It affects 1% of the population and is characterized by inflammation and destruction of the joints; inflammation is typically located in the hand and foot joints, but other joints are also regularly inflamed. Pain, stiffness, activity limitation, and functional disability are direct consequences of inflammation and have an impact on physical functioning on the individual level and result in work loss. These disease aspects are the worst at the time of RA diagnosis and do not revert to normality when treatment is initiated during the phase of clinical arthritis [1–3]. This causes a large burden of costs for society; direct costs have considerably escalated due to expensive therapies, and indirect costs are due to sick leave, work loss, and disability pensions [4]. New biologic drugs and better treatment strategies have resulted in improved disease outcomes during the last decades, and clinically relevant joint destruction has become infrequent. However, RA patients still have a chronic disease and RA remains a remitting and relapsing condition that cannot be cured. The ultimate treatment strategy prevents the development of persistent RA.

The mechanisms underlying arthritis becoming chronic are poorly understood. The development of RA is considered to be a multiple-hit process that is largely taking place before the disease presents with clinically swollen joints. Different phases in the development of RA are described by a “European League Against Rheumatism” (EULAR) taskforce [5, 6]; the phase that precedes the development of clinically apparent arthritis is a phase of symptoms. The pattern of symptoms that characterizes this pre-arthritis phase has been called clinically suspect arthralgia (CSA) [7]. The clinical expertise (relying on pattern recognition) of rheumatologists has been shown accurately in the identification of patients with arthralgia at risk for RA among all patients with arthralgia presenting to secondary care (odds ratio 55, sensitivity 80%, specificity 93%) [8]. In this phase of CSA, patients have not only symptoms such as pain and stiffness but also functional limitations [9]. Sick leave and disability pensions are described to rise 6 months before the diagnosis [4]. Additionally, patients can have maturing auto-antibody response or increased levels of pro-inflammatory cytokines in the systemic circulation [10, 11]. Together, these findings illustrate the relevance of the CSA phase from the patients’ perspective and the immunological perspective.

Although clinical joint swelling is per definition absent in CSA, patients can have subclinical joint inflammation in the hands or feet, that is, synovitis, tenosynovitis, and/or inflammation of the subarticular bone, also called osteitis or bone marrow edema (BME). Magnetic resonance imaging (MRI) is a sensitive tool to detect subclinical joint inflammation. Furthermore, the definition of the presence of (“positivity for”) subclinical joint inflammation was established by the generation of a reference atlas from persons from the general population [12, 13]. Including information on MRI findings from age-matched symptom-free persons (same feature, same anatomic location), a highly specific definition was obtained without losing sensitivity. The presence of subclinical inflammation in patients with CSA is associated with a risk of 32% to progress to RA during the next year [14]; the NPV is 93%, indicating an acceptable ability to detect RA in a symptomatic pre-arthritis phase and a low chance to miss patients because of false-negative results.

The risk of progression to clinical arthritis and RA is an ongoing research area. At present, no internationally validated prediction model is available. Patients with CSA have a higher risk of RA development than patients with non-specified musculoskeletal symptoms [15]. In addition to subclinical inflammation, the presence of auto-antibodies (anti-citrullinated peptide antibody (ACPA) and rheumatoid factor (RF)) is associated with the development of clinical arthritis [16]. The data on the predictive value of ACPA levels are contradictory [16]. Also, the predictive value of inflammatory response proteins measured in the systemic circulation is unclear; most research has so far been conducted on C-reactive protein (CRP), which is routinely measured in the clinic, but its predictive value in arthralgia is not undisputed [16]. Thus, the presence of imaging-detected subclinical inflammation and auto-antibodies are two validated and independent risk factors in CSA. Importantly, MRI-detected subclinical inflammation yields elevated PPVs for RA development also in ACPA-negative CSA patients [17, 18].

There are five other placebo-controlled trials aiming at secondary prevention, namely PRAIRI (2009-010955-29), APIPPRA (2013-003413-18), ARIAA (2014000555-93), and STAPRA (2013-05524-42) reported on www.clinicaltrialsregister.eu, and StopRA (NCT02603146) reported on www.ClinicalTrials.gov. STAPRA has been stopped prematurely, which studied the effect of intervention with statins. The other ongoing trials study the effectiveness of intervention with biologic disease-modifying anti-rheumatic drugs (DMARDs). All mentioned trials include participants positive for auto-antibodies. The TREAT EARLIER trial will include patients with CSA irrespective of the auto-antibody status. While ACPA-positive has always been a more severe subset of RA, up-to-date treatment strategies have made the disease burden comparable in many aspects for ACPA-positive and ACPA-negative patients with RA [19]. This implies that efforts to further improve the disease outcomes should be proportional to both disease subsets. Furthermore, for the management of early arthritis, EULAR recommends methotrexate (MTX) as the first-line therapy, possibly combined with a short course of corticosteroids, independent of the auto-antibody status [20]. Based on observations done in patients with classified RA (in both APCA-positive and ACPA-negative RA) that the time to intervention determines the efficacy of intervention [21] and the fact that subclinical joint inflammation can now be detected in patients with CSA, we hypothesize that intervention with the cornerstone and first-line therapy of RA in this pre-arthritis phase is effective in preventing arthritis becoming chronic (“chronification”). The present proof-of-concept study will test this hypothesis with our ultimate goal to reduce the disease burden of RA.

### Objectives {7}

We hypothesize that intervention in the pre-arthritis phase of CSA with subclinical joint inflammation is effective in preventing arthritis from becoming chronic (“chronification”). The present proof-of-concept study will test this hypothesis with our ultimate goal to reduce the disease burden of RA (Fig. 1).

**Fig. 1 Fig1:**
[figure not shown]
Schematic figure of the objective of the TREAT EARLIER trial

### Trial design {8}

The present study concerns a randomized placebo-controlled, parallel, double-blind, superiority clinical trial (RCT) comparing an 1-year course of MTX combined with a single glucocorticoid intramuscular (IM) depot injection, with a combination of oral and IM placebo in patients who are deemed to be at high risk of developing RA because of having recent-onset CSA and MRI-detected subclinical inflammation (Fig. 2). Participants will be treated for 1 year and followed for another year to observe the development of clinically detectable arthritis, either fulfilling the 2010 criteria for RA [22] or unclassified clinical arthritis with a 66-swollen joint count (SJC) of ≥ 2, which persist for at least 2 weeks. Participants who reach the primary endpoint will be treated according to the general rheumatologic care and in line with the Dutch and international guidelines [23].

**Fig. 2 Fig2:**
[figure not shown]
Overview of the TREAT EARLIER study

## Methods: study setting, participants, and criteria

### Study setting {9}

The Leiden University Medical Center (LUMC, The Netherlands) is the only center where participants will be enrolled in this single-center study. Screening with MRI will be done in the LUMC, and for the duration of the trial, all participants will be treated in the LUMC. This is done for practical reasons; it allows consistency in the use of MRI (same protocol, same scanner, same readers) in a patient-friendly manner because of excellent accessibility to MRI in the LUMC. It also allows consistency in the determination of endpoints because all data are collected by a group of rheumatologists and research nurses that were trained together.

Despite the fact that the trial will be performed in one center, recruitment will be done in the South-West region of The Netherlands. Rheumatologist in all hospitals in this region (for a list, see supplementary file 2) have agreed to inform all eligible patients with CSA on the TREAT EARLIER trial and, with the consent of the patient, to transfer the patient’s contact details to the study doctor in the LUMC (Fig. 3). The study doctor, who should have obtained the medical doctor degree (MD) and is working as a PhD student at The Department of Rheumatology within the LUMC, is then responsible for the screening process. The participation of the total region is an important success factor to identify enough patients in this very early phase, because patients presenting with CSA are relatively infrequent as the majority of patients already present with swollen joints. Importantly, our long-standing efforts to allow very early access for patients with CSA [24] and the commitment of all hospitals in the region allows to screen and include sufficient participants in this trial.

**Fig. 3 Fig3:**
[figure not shown]
Screening of eligible patients in the southwest region of The Netherlands

### Eligibility criteria {10}

We use a two-level definition to identify patients that are prone to develop RA. First, patients need to have arthralgia that is suspect to progress to RA according to the treating rheumatologist, and second, patients should have a 1.5-T MRI showing local subclinical inflammation (Fig. 3).

#### Clinically suspect arthralgia

No single symptom is highly characteristic and specific for a preclinical phase of RA. However, patients with symptoms at risk for the development of RA, in the absence of clinical arthritis, can be identified by rheumatologists using pattern recognition. This symptom complex is also called CSA [25]. For inclusion in our trial, participants need to have CSA, which is arthralgia of the small joints and of recent onset (symptoms < 1 year) that according to the judgment of experienced rheumatologists are suspect to progress towards RA over time. The presence of symptoms or signs that make other diagnoses more likely rules out CSA. We previously demonstrated that only 6% of all patients that presented with arthralgia to the rheumatology outpatient clinic of the LUMC had CSA, and the clinical expertise had an odds ratio of 55 for identification of patients at risk for RA [8].

The recognition of the symptom complex that is described as CSA followed the identification of different disease phases that precede the development of RA by the EULAR taskforce in 2012 [5]. According to this model, there are genetic and environmental risk factors that play a role where patients are initially asymptomatic; thereafter, symptoms occur and eventually, clinical arthritis develops. After the recognition of CSA, a subsequent EULAR taskforce has derived a definition of arthralgia suspicious for the progression of RA. This definition was derived in 2016 and validated thereafter [7, 26]. The TREAT EARLIER trial was designed in 2014, and therefore, patients with CSA need to be identified by rheumatologists using their pattern recognition, but the fulfillment of the EULAR definition is not a requirement as this definition did not exist at the study start.

Hence, CSA is identified based on clinical symptoms and signs at the first presentation to the outpatient clinic. The results of laboratory investigations are not required for the identification of CSA. Moreover, laboratory assessments are generally not performed by our general practitioners, as according to the Dutch guidelines for primary care general practitioners are discouraged to perform these tests (https://www.nhg.org/standaarden/volledig/nhg-standaard-artritis).

#### MRI-detected subclinical inflammation in small joints

Secondly, CSA patients need to have an MRI positive for subclinical inflammation, which is inflammation that is present in < 5% of the age-matched general population, according to two independent readers blinded to clinical data.

#### MRI protocol

The screening MRIs will be made of the unilateral wrist, metacarpophalangeal (MCP)2–5 joints, and metatarsophalangeal (MTP)1–5-joints at the most painful side, or the dominant side in case of equally severe symptoms. MRIs will be performed on a musculoskeletal (MSK) 1.5-T MRI system (GE, WI, USA) using a 145-mm coil for the foot and a 100-mm coil for the hand at the Department of Radiology of the LUMC. The participants are positioned in a chair beside the scanner, with the hand or foot fixed in the coil with cushions. For a detailed scan protocol, refer to supplementary file 3.

The MRIs will be scored for synovitis, tenosynovitis, and BME (osteitis). Synovitis and osteitis are scored according to the “outcome measures in rheumatology clinical trials” (OMERACT)-RA MRI scoring (RAMRIS) system [27], which is adopted to also include the MTPs. Tenosynovitis in the MCP, MTP joints, and the wrist, with post-contrast sequences, is scored as described by Haavaardsholm et al. [28]. Contrast enhancement around the extensor tendon sheaths in the MCPs are scored according to this method [29, 30]. For a detailed overview, refer to supplementary file 4.

#### MRI reading

To have two trained MRI readers that are available all days to drop their work immediately when an MRI is made to prioritize MRI scoring, every day a week during the expected inclusion duration of 5 years, we have trained 10 MRI readers. All readers have become experienced; they have undergone a training period of 6 months of almost daily MRI reading and have scored hundreds of MRIs from CSA and early arthritis patients as well as healthy controls before finishing the training period. The interreader and intrareader intraclass correlation coefficients (ICCs) are all > 0.90 (supplementary file 5). Furthermore, during the screening period, they will repeatedly determine their intrareader ICCs.

##### Inclusion criteria

Age ≥ 18 years.Patients without clinically detectable arthritis but with arthralgia of the small hand or feet joints of recent onset (< 1 year) that according to the rheumatologist is suspect to be an early presentation of RA (this symptom complex is called CSA).Unilateral MRI of the hand and foot joints, positive for subclinical inflammation.Ability and willingness to give written informed.

##### Exclusion criteria

Symptoms or signs making diagnoses other than RA more likely. These are among others; > 6 tender points or Heberden or Bouchard nodules (the presence of such characteristics precludes CSA).Presence of, or history of, clinically apparent arthritis (this precludes CSA).Previous or current treatment with DMARDs or corticosteroids (this precludes CSA).Contraindications for MRI: certain metal implants, pacemakers, GFR < 30 ml/min.Pregnancy or the wish to become pregnant, breastfeeding.Bone marrow hypoplasia.Elevated hepatic enzyme levels (ASAT, ALAT > 3 times normal value).Serum creatinine level > 150umol/l or estimated clearance of < 60%.Serious infections such as hepatitis, pyelonephritis in the past 3 months, or chronic infectious diseases such as chronic chest infections with bronchiectasis.

### Who will take informed consent? {26a} and additional consent provisions for collection and use of participant data and biological specimens {26b}

Informed consent will be obtained by research nurses, who are Good Clinical Practice (GCP)-certificated. Informed written consent for screening MRIs will be obtained from all eligible CSA patients (Fig. 3). In case the MRI scan is positive and patients are willing to participate in the trial, the trial informed consent will be signed.

## Methods: interventions

### Explanation for the choice of comparators {6b}

There is no biological data on the mechanisms involved in the “chronification” of arthritis, and scientific evidence to prioritize one specific DMARD is therefore lacking. The EULAR recommendation for the management of RA suggests the use of MTX with or without glucocorticoids as the first choice induction therapy for patients with newly diagnosed RA [23]. MTX in a dosage of ≥ 20 mg/week with folate substitution has become the anchor drug for RA because of its efficacy [20, 31–34], acceptable toxicity profile, and higher retention rate than other DMARDs. MTX is the anchor drug for RA; it has a favorable benefit/risk ratio and is cheap; we propose to study the effectiveness of MTX in patients with CSA. EULAR guidelines for the treatment of RA are similar for auto-antibody-positive and auto-antibody-negative RA patients [20]. Likewise, intervention in the TREAT EARLIER trial will not be stratified for auto-antibody status.

Whether IM corticosteroids are disease-modifying drugs is a matter of debate. They can reduce radiological progression; whether they are able to modify the persistency of the disease is not clear. The SAVE trial showed no effect of a single glucocorticoid injection on the disease course [35], whereas the STIVEA trial reported that a 3-week course of IM glucocorticoid injections resulted in a significantly higher rate of DMARD-free sustained remission compared to placebo injections [36]. These data may indicate that the effect of one or a few IM corticosteroid injections, without subsequent DMARD therapy, on arthritis persistence is not large. In clinical trials such as the FINRA-Co study and the BeSt study, however, it has been demonstrated that combination therapy of MTX with oral prednisone is superior in early symptom suppression and prevention of radiological damage compared to MTX monotherapy. The tREACH trial showed that in undifferentiated arthritis, the initial treatment with a combination of MTX with corticosteroids was also superior to MTX monotherapy, without a difference between oral prednisone or an IM depot injection [37]. The additive effect of low-dose corticosteroids to conventional DMARDs was also described in a recent systematic literature review [38]. Based on these observations, EULAR guidelines recommended that corticosteroids can be added at the start, especially as MTX is slow acting and a short course of corticosteroids can have a rapid effect. Moreover, it has been shown that this addition does not affect safety [39]. Thus, in line with previous and current EULAR recommendations of the management of RA [20, 23, 33], in the current trial, corticosteroids will be added to MTX in the form of a single IM depot injection at the start of MTX.

### Intervention description {11a}

In this double-blind RCT, participants will be randomized to two arms in an 1:1 ratio. The randomization consists of one IM glucocorticoid injection (120 mg methylprednisolone or IM placebo injection) followed by 12 months of MTX tablets (or placebo tablets) (Fig. 2). No other corticosteroid interventions will be allowed during the trial, unless participants have reached the primary endpoint and proceeded to open-label DMARD therapy.

MTX (or placebo) tablets will be increased in 4 weeks to 10 tablets/week (25 mg/week). Open-label folic acid supplementation (5 mg/week) will be added, in line with the Dutch guidelines of MTX use (https://www.nvr.nl/richtlijnen/nvr-richtlijnen-standpunten-en-zorgpaden/). After 45 weeks of 10 tablets/week (MTX or placebo), tablets will be tapered for 4 weeks and then stopped at week 53. Participants will be followed for another 12 months.

### Criteria for discontinuing or modifying allocated interventions {11b}

Laboratory tests to monitor possible side effects of MTX will be performed according to the Dutch guidelines of MTX (https://www.nvr.nl/richtlijnen/nvr-richtlijnen-standpunten-en-zorgpaden/). In case of mild side effects of MTX, either symptom experienced by the participants or abnormalities in the laboratory tests (mild increase in ASAT, ALAT, or mild decrease of leucocyte or thrombocyte counts), the dosage will be decreased to 5 mg (2 tablets/week), until an acceptable status is obtained. In case the dosage will be less than 3 tablets/week (< 7.5 mg MTX/week), MTX is stopped as in daily practice dosages lower than 7.5 mg/week is considered not effective. Then, participants will be treated according to the treating rheumatologist opinion, however not with DMARDs or corticosteroids as this would be a protocol violation. In case of severe side effects, the treating rheumatologist will stop the MTX (or placebo). Also, this is in line with the Dutch guidelines and with the common practice of MTX treatment in RA. The intention of the trial is to follow all participants for the total trial period of 24 months. Participants who need to stop the study medications because of toxicity (or other reasons, e.g., wish of participant) will be asked to remain in the trial for the entire follow-up period.

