### Strategies to improve adherence to interventions {11c}

MTX is considered as a chemotherapy medication (despite the low dose of the tablets of 2.5 mg each), and therefore, it is not allowed for researches to count tablets at the moment of tablet distribution and return, according to our pharmacy guidelines. Therefore, participants will be asked to complete a medication diary in order to monitor medication adherence, which will be done for study medication and concomitant non-steroidal anti-inflammatory drugs (NSAIDs) use (and will be reviewed every visit).

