## Statistical methods

### Statistical methods for primary and secondary outcomes {20a}

All statistical methods for the primary and secondary endpoints will be described in the statistical analysis plan, which will be completed and submitted before unblinding. Analyses will be based on the intention-to-treat (ITT) and per-protocol (PP) population. The ITT population will consist of all participants randomly assigned to a treatment group. The ITT population will form the primary analysis population of the trial and will be used for all primary and secondary efficacy endpoints and for safety analyses. This strategy is conservative because it tends to underestimate the difference in the outcome between the treatment groups, but it respects the randomization process, is free from bias, and resembles clinical practice. The PP population will consist of all participants meeting the study entry criteria, who completed follow-up and who in the first year after randomization, or up to a primary event in this period, have used ≥ 8 study tablets a week (equivalent to at least 20 mg/week MTX) for 80% of the time and used no forbidden medication (no systemic or intra-articular steroids or DMARDs outside the study protocol) during the entire follow-up period. An MTX dose of ≥ 20 mg/week has been shown to provide optimal efficacy in RA [31, 32, 34]; therefore, a dose of ≥ 8 study tablets was incorporated in the definition. The PP population will consist of participants who strictly adhere to the protocol and provide an estimate of the true efficacy of the MTX intervention. All primary and secondary efficacy endpoints will also be analyzed in the PP population. The primary analysis will be the time to the development of the primary endpoint. The co-primary endpoint is the difference in the percentage of patients that achieved DMARD-free status at 24 months. Significance will be assessed by a gate-keeping analysis. We do prioritize the two primary endpoints by testing the primary endpoint first, and only if this test is significant, the co-primary endpoint will be tested.

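### The dose-modification rule in {11b} contradicts itself: the reduction prescribed for mild side effects falls below the dose at which the next sentence stops methotrexate

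*Protocol article*

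**What the plan says.** Three instructions on study-drug exposure follow one another in the protocol article, section {11b}.

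- **Mild toxicity.** The trigger is broad: "In case of mild side effects of MTX, either symptom experienced by the participants or abnormalities in the laboratory tests". The examples given are mild rises in liver enzymes and mild falls in white-cell or platelet counts. The action is that "the dosage will be decreased to 5 mg (2 tablets/week), until an acceptable status is obtained".
- **Lower limit.** The very next rule is "In case the dosage will be less than 3 tablets/week (< 7.5 mg MTX/week), MTX is stopped". The reason given is that smaller weekly doses are regarded as ineffective in daily practice. After such a stop, other DMARDs and corticosteroids remain forbidden.
- **Severe toxicity.** A separate sentence has the treating rheumatologist stop the study drug.

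The same section, and section {18b} on retention, ask anyone who comes off study tablets to stay in follow-up to month 24. Section {11a} sets the target at 10 tablets (25 mg) a week. Section {20a} makes intention-to-treat the primary population. It admits to the per-protocol set only those who, in year 1 or up to a primary event in that year, took eight or more "study tablets a week (equivalent to at least 20 mg/week MTX) for 80% of the time".

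**The concern.** The first two instructions cannot both be followed. A clinician who carries out the mild-toxicity step has put the participant in the zone where the next sentence requires a stop. The rule then makes no distinction between mild and severe toxicity, although the section clearly sets out to make one.

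This matters statistically because the rule governs exposure to the study drug. The listed events are known effects of methotrexate, so they are likely to be more frequent in the active arm. If the text is applied literally, study drug could end more often in that arm for minor events. That would pull the intention-to-treat contrast toward no difference and would change who satisfies the per-protocol exposure rule. If the text is not applied literally, a reader of the article cannot tell what was done instead.

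**Working it through.** **Step 1: rule out a unit or conversion slip.** Section {11c} gives the tablet strength: "despite the low dose of the tablets of 2.5 mg each". Weekly dose = tablets per week × 2.5 mg.

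| Rule | Tablets/week | × 2.5 mg | Stated in article |
|---|---|---|---|
| Target dose {11a} | 10 | 25 mg | 25 mg |
| Per-protocol threshold {20a} | 8 | 20 mg | 20 mg |
| Stopping limit {11b} | 3 | 7.5 mg | 7.5 mg |
| Reduced dose for mild toxicity {11b} | 2 | 5 mg | 5 mg |

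All four pairs reproduce. The conflict is between the rules, not within a conversion.

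**Step 2: compare the reduced dose with the limit.** 2 < 3 tablets, and 5 < 7.5 mg. The reduced dose is a fixed number, so the result does not depend on the dose the participant was taking before. From target, the step is a cut of (25 − 5)/25 = 80%, ending one tablet below the stopping limit.

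**Step 3: follow the rule through.** Mild event → 2 tablets → below 3 tablets → stop. Severe event → stop. Both paths end in the same place, and there is no period in which a reduced dose can be held until status is acceptable.

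**Step 4: look for a resolving statement elsewhere.** The article contains no exemption for temporary reductions and no other reduction scheme. Sections {11b} and {11d} refer to the Dutch methotrexate guideline for toxicity monitoring, but its content is not reproduced, so it cannot be used to settle the point.

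**Step 5: see where the per-protocol set is sensitive.** Section {11a} gives a 4-week increase, 45 weeks at 10 tablets and a 4-week taper. I take the year as W = 52 or 53 weeks. The weekly steps are not stated, so I assume that k = 0 to 2 of the increase and taper weeks reach 8 tablets (at most one of each).

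Tolerated weeks below 8 tablets, within the full-dose period = 45 + k − 0.8 × W.

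- W = 53, k = 0: 45 − 42.4 = 2.6 weeks.
- W = 52, k = 2: 47 − 41.6 = 5.4 weeks.

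For a participant without a primary event in year 1, an interruption of up to roughly 3 to 5 weeks is therefore compatible with the per-protocol set. A permanent stop is compatible only if nearly all the full-dose weeks are already done. With no taper weeks to count and at most one increase week, the requirement runs from 41.6 − 1 = 40.6 to 42.4, that is 41 to 43 of the 45 whole weeks. The two readings of {11b} thus give different per-protocol membership for participants whose mild event would otherwise have meant a short reduction. A longer reduction below 8 tablets excludes under either reading.

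**The case against.** The best defence is that the literal reading is the least plausible one. The phrase about reaching an acceptable status, the separate lower limit and the separate sentence for severe events fit together only if mild toxicity was meant to lead to something short of a stop. That points to a slip of wording in a condensed article, and the full protocol, which is not shown, may read differently. This is a fair account of how the conflict may have arisen. It does not remove the conflict: the article states a rule with tablet counts, and the counts are incompatible.

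Several stronger readings are tempting and are not supported.

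- *A reader might infer a head count of methotrexate participants taken off drug*, by applying some toxicity rate to the 115 per arm. The article gives no rate of mild side effects, so any such figure would reflect only the rate assumed.
- *A reader might infer that the contradiction strips the active arm out of the per-protocol set.* Much of that loss comes from the 8-tablet definition itself, however {11b} is reconciled. Only short reductions are treated differently.
- *A reader might infer that the randomised comparison is biased, or that participants are lost.* Those who stop tablets are asked to continue visits, and intention-to-treat is primary. The risk is dilution and lost power.
- *A reader might infer wide variation between clinicians.* All participants are treated in one centre with reference to a national guideline. Differing practice is possible but not shown.

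**Conclusion.** The point stands as an internal contradiction in a stated rule for study-drug exposure. The step for mild side effects always meets the stopping condition, so the text as written ends study medication (not trial participation) for mild and severe events alike. The conclusion needs only the tablet counts in {11b}, which agree with the tablet strength in {11c}.

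The certain size is small and exact: the written reduced dose lies one tablet (2.5 mg) a week below the stopping limit. The effect on the trial is a direction, not a number. Literal use could end study drug more often in the methotrexate arm, dilute the intention-to-treat contrast, and alter per-protocol membership for participants with short-lived mild toxicity. This rests on two assumptions: that the listed events are more frequent on methotrexate, and that the rule was applied as printed. Neither can be quantified from the article. A wording error remains possible, and it should be corrected because nothing in the article does so.

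**What to change.** The sponsor should check the two sentences in {11b} against the full protocol and reconcile them into one consistent rule. That rule should be communicated to the treating rheumatologists and the pharmacist. The sponsor should also record, before unblinding, which rule was actually applied during the trial, so that exposure and per-protocol membership can be interpreted. Which dose or rule is right is a clinical matter on which this review takes no position.

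The cost is a correction to two sentences, a short clarification to the trial staff and a dated note to file. Sample size, visits and planned analyses do not change.
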